## Summary of Changes from Previous Version 1.0:

| Affected Section                   | Summary of Revisions Made                                                                                                                                                                                                                                                                                                                              | Rationale                                                                                                                                              |
|------------------------------------|--------------------------------------------------------------------------------------------------------------------------------------------------------------------------------------------------------------------------------------------------------------------------------------------------------------------------------------------------------|--------------------------------------------------------------------------------------------------------------------------------------------------------|
| Section 1                          | Short title has been revised                                                                                                                                                                                                                                                                                                                           |                                                                                                                                                        |
| Section 1 & 5.1                    | Inclusion criteria have been revised                                                                                                                                                                                                                                                                                                                   | For children aged 4-6 years old without past prescription forms, eligibility requires myopia below the 3 rd percentile on refraction curves |
| Section 1 & 6.2                    | The selection of eye for statistical analysis has been revised                                                                                                                                                                                                                                                                                         | To provide a detailed description of the data selection for statistical analysis                                                                       |
| Section 2                          | New visits, V5a & V5b, have been incorporated in the Study Plan Schematic, and conditions regarding lens changes have been                                                                                                                                                                                                                             | To revise the Study Plan Schematic and provide a detailed description on conditions of lens changes                                                    |
| Section 5.1                        | A decision tree for selecting a valid past prescription form has been incorporated                                                                                                                                                                                                                                                                     | To offer a clear guideline on the selection of eligible past prescription form                                                                         |
| Section 5.11                       | 
 
- Clinical devices for measuring pupil size and IOP has been revised
 
- Measurement of BCVA has been updated
 
- Eyedrop for cycloplegia has been updated
 
- Measurement of peripheral refraction has been updated
 
- Measurement of ocular biometry has been deleted
 
 | To streamline data collection procedures and update measurement methods based on clinical needs                                                        |
| Section 5.14                       | Data collection time points for choroidal thickness and vision performance questionnaire have been updated                                                                                                                                                                                                                                             | To clearly outline the data collection time points for each measurement                                                                                |
| Section 5.15, 5.16, 5.17.2, 5.17.3 | New visits, V5a & V5b, have been incorporated                                                                                                                                                                                                                                                                                                          | To describe the study visits more accurately                                                                                                           |
| Section 5.17                       | The record forms used in each study visit has been updated                                                                                                                                                                                                                                                                                             | To describe the record forms used more accurately                                                                                                      |
| Section 5.18, 14.1                 | The record forms used in protocol violation have been updated                                                                                                                                                                                                                                                                                          | To describe the record form used more accurately                                                                                                       |
| Section 1, 6.1 & 6.2               | Sample size and statistical analysis have been revised                                                                                                                                                                                                                                                                                                 | To introduce an interim analysis                                                                                                                       |

|                     |                                                                                                           |                                                                                               |
|---------------------|-----------------------------------------------------------------------------------------------------------|-----------------------------------------------------------------------------------------------|
| Section 8.6         | The procedures of data monitoring have been updated                                                       | More stringent monitoring has been implemented                                                |
| Section 11.1        | Disclosure of group allocation and thank-you letter to subjects after completion of study has been added. | To provide more detailed description of the actions upon study completion                     |
| Study Title         | The full study title has been revised                                                                     | To align the product name with that used in previous publications                             |
| Section 5.12 & 5.13 | Timepoint for the main outcome measures has been revised                                                  | To correct the typographical error                                                            |
| Section 5.14        | Timepoints for choroidal thickness measure has been revised                                               | To introduce additional measurement timepoint to account for the lens change in control group |
| Study title         | The full and short study titles have been revised by changing the word “Effectiveness” to “Efficacy”      | “Efficacy” is more precise for a controlled clinical trial setting                            |
| /                   | Abbreviation of second-generation DIMS lens has been revised from “DG2” to “D2”                           | A simplified abbreviation is suggested by sponsor                                             |
| Section 1           | The funding source has been amended                                                                       | To correct the errors in previous version                                                     |
| Section 1 & 6.1     | Sample size calculation has been amended                                                                  | To correct the errors in previous version                                                     |

**Anticipated commencement date: Aug 2023**

**Anticipated end date: Sep 2026**

## **1. Overview**

### **Title of study**

Myopia Control Efficacy of Second-generation Defocus Incorporated Multiple Segments Spectacle Lenses on Fast Progressing Myopes: A Randomised Controlled Trial

### **Short title**

Efficacy of DIMS on Fast Progressing Myopes

### **Study description and methodology**

Myopia is a widespread concern of global significance; however, it remarkably impacted many East Asian populations, including Hong Kong. The prevalence of myopia in 8-year-old Hong Kong children has reached approximately 40%. In most cases, myopia developed in early childhood will progress until late adolescence. As our population ages, it is projected that more than 80% of the population will become myopic, of whom 10% will be highly myopic. Notably, high myopia is associated with the increasing risk of sight-threatening eye diseases, such as glaucoma, retinal detachment, choroidal neovascularization and myopic macular degeneration. It can cause an increasingly high socio-economic burden to the health care system and society.

Various interventions have been implemented to halt myopia progression in children, yielding efficacy rates ranging from 15% to 60%. The clinical application of myopic defocus in conjunction with spectacle correction, through the Defocus Incorporated Multiple Segments (DIMS) technology, has demonstrated to be a viable and effective method for slowing down the progression of myopia in children. However, DIMS spectacle lenses (first generation, D1) reduced myopia progression by 52% and axial elongation by 62% in children aged 8-13 years may not convincingly reflect the technology's effectiveness on fast progressing myopes and younger myopes. PolyU and spectacle lens manufacturer (HOYA Corporation, Tokyo, Japan) jointly designed

the second generation of DIMS lens (D2) that aims to provide a higher effectiveness than the first-generation lens.

The aim of this Randomised Clinical Trial (RCT) is to validate the efficacy of the first and second generation of DIMS lenses (D1 & D2) to reduce myopia progression for fast progressing myopic children aged 4-12 years. To investigate factors affecting myopia control efficacy between individuals, relative peripheral refraction (RPR) and choroidal thickness measurements are also conducted.

## **Objective**

Primary:

- i. To determine the efficacy of D2 lens design in slowing myopia progression in children with fast progressing myopia as compared to the single vision (SV) control.

Secondary:

- i. To determine the efficacy of D1 lens design in slowing myopia progression in children with fast progressing myopia as compared to SV control.
- ii. To investigate if baseline RPR influences the outcome of myopia control when using DIMS lenses.
- iii. To determine if the change of choroidal thickness following short-term DIMS lens wear has a prognostic value in determining the efficacy of myopia control over one year.

## **Study population**

One hundred and seventy-seven fast progressing myopic children between the ages of 4 to 12 years will be recruited. They will be stratified by 3 age groups: 4-6, 7-9 and 10-12, in a ratio of 1:2:1.

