## Statistical methods

### *Sample Size Calculation*

To achieve a 90% power to detect a 0.315D difference and standard deviation of 0.475D (effect size of 0.658) in SER progression between a treatment group and a control group with an alpha level of 0.05 (2-tailed); the minimum subject number required in each group is 50.

An interim analysis will be performed to evaluate the efficacy on primary and second outcomes at 6 months. To compensate the impact on the final efficacy analysis, Bonferroni adjustment will be performed and the adjusted alpha level will be 0.025. Accordingly, the subject number required in each group is 59 at a 90% power. Assuming a dropout rate of about 10%, at least 65 subjects are required in each group.

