### **5.6.2. Phase 2: Auxiliary group**

To compare the efficacy and visual performance of D1 and D2 lenses for internal reference, an auxiliary group having the same number of subjects will be assigned to wear D1 lenses for 2 years. Recruitment criteria, measurement and follow-up intervals of the auxiliary group will be the same as in Phase 1 study.

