## **5.7. Randomisation**

Simple randomisation will be implemented by an unmasked Investigator by creating a column of random numbers for the group allocation using Microsoft Excel. Eligible subjects will be assigned to one of the three groups in an equal ratio by following the random sequence generated from Excel. Age will be stratified by 3 groups: 4-6, 7-9 and 10-12, in a ratio of 1:2:1.

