## 6. Statistical Considerations

### 6.1. Sample Size Calculation

To achieve a 90% power to detect a 0.315D difference and standard deviation of 0.475D (effect size of 0.658) in SER progression between a treatment group and a control group with an alpha level of 0.05 (2-tailed); the minimum subject number required in each group was 50.

An interim analysis will be performed to evaluate the efficacy on primary and second outcomes at 6 months. To compensate for the impact on the final efficacy analysis, Bonferroni adjustment will be performed with an adjusted alpha level of 0.025. Accordingly, the subject number required in each group is 59 at a 90% power. Assuming a dropout rate of about 10%, at least 65 subjects are required in each group.

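### The Overview's recruitment total of 177 is three times 59, with no dropout allowance, and contradicts the protocol's own requirement of at least 65 per group (195)

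*Protocol*

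**What the plan says.** Section 1 (Overview), Study population, gives the enrolment total: "One hundred and seventy-seven fast progressing myopic children between the ages of 4 to 12 years will be recruited".

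The sample size text appears in the Overview and again in section 6.1. It starts from 0.315 D and a "standard deviation of 0.475D (effect size of 0.658"), and finds 50 per group at two-sided alpha 0.05. It then lowers alpha to 0.025 because of the 6-month interim analysis: "Accordingly, the subject number required in each group is 59 at a 90% power". Last comes the dropout step: "Assuming a dropout rate of about 10%, at least 65 subjects are required in each group".

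Section 5.7 sets the number of groups: "Eligible subjects will be assigned to one of the three groups in an equal ratio". Section 5.6.2 gives the D1 arm the same size as the others: "an auxiliary group having the same number of subjects will be assigned to wear D1 lenses for 2 years". Section 6.2 fixes the significance level of all analyses at 2.5%, two-tailed.

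**The concern.** A recruitment total should be the dropout-inflated group size times the number of groups. Here it equals the uninflated group size times three, so the last step of the sample size calculation did not reach the Study population paragraph.

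The recruitment total tells the study team, the ethics committee and readers when enrolment is complete. A team that stops at 177 follows the Study population paragraph and breaches the minimum in section 6.1. The primary comparison (D2 against single vision, change in SER over 12 months) would then rest on fewer completers than the 90% power claim assumes.

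**Working it through.** **Inputs, all from the protocol.** Difference 0.315 D, SD 0.475 D, stated effect size d = 0.658, power 90%, two-sided alpha 0.05 and then 0.025, 59 per group evaluable, about 10% dropout, at least 65 per group recruited (section 6.1); total 177 (Overview); three equal groups (sections 5.6.2 and 5.7).

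**Method.** Unpaired t-test with equal groups of n. Degrees of freedom are 2n − 2 and the noncentrality is d × √(n/2). Power is the probability that a noncentral t variable exceeds the two-sided critical value in absolute size.

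**Step 1. Reproduce the protocol's group sizes.** With d = 0.658, the smallest n reaching 90% is 50 at alpha 0.05 and 59 at alpha 0.025 (power 90.2% at 59). Both stated figures reproduce exactly.

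**Step 2. The dropout step.**
- 59 × 1.10 = 64.9, rounded up to 65, the stated figure.
- 59 / 0.90 = 65.6, rounded up to 66, by the usual formula.
- 65 × 0.90 = 58.5 completers per group.

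**Step 3. The totals.**
- 3 × 59 = 177, the Overview total.
- 3 × 65 = 195, the total that section 6.1 implies.
- Shortfall: 3 × 6 = 18 children overall, of which 2 × 6 = 12 are in the primary comparison and 6 in the D1 group.

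**Step 4. Power at two-sided alpha 0.025.**

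| Recruited per group | Loss | Completers per group | d = 0.658 | d = 0.663 |
|---|---|---|---|---|
| 59 (total 177) | none | 59 | 90.2% | 90.7% |
| 59 (total 177) | 10% | 53 (59 × 0.90 = 53.1) | 86.5% | 87.1% |
| 65 (total 195) | 10% | 58.5 | 89.9% | 90.4% |

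The 10% rows assume that a child who drops out adds nothing to the comparison. For the middle row, a normal approximation gives 87.4% and 88.0%, so the choice of method does not change the picture.

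**Step 5. The effect size.** 0.315 / 0.475 = 0.663. Rounding of the displayed inputs does not explain 0.658, because the lowest ratio they allow is 0.3145 / 0.4755 = 0.661. The stated 0.658 would need an SD of 0.315 / 0.658 = 0.479. With d = 0.663 the required n is 49 at alpha 0.05 and 58 at alpha 0.025, one fewer than stated in each case. Then 58 / 0.90 = 64.4, so 65 per group still follows.

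**The case against.** **177 might be meant as something else.** A two-group total does not fit: 177 is odd, and two groups make 118 at 59 each or 130 at 65 each. Nor is it described as a number of completers, since the sentence speaks of recruitment. The contradiction stands.

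**The power loss may be smaller than computed.** This is the best counter-argument, and part of it stands. Section 6.2 plans an intention-to-treat analysis with multiple imputation, so a child with 6-month data may still contribute something. Section 5.9 allows replacement of randomised children who were never treated, and of some who leave in the first month while recruitment is open. How much either recovers cannot be calculated from the protocol. Against this, section 5.9 also ends data collection at withdrawal, replacement does not cover ordinary attrition up to 12 months, and the sample size calculation itself takes no credit for imputation. So 86.5% to 87.1% should be read as the value when dropouts contribute nothing, and 90.2% to 90.7% as the value with no net loss.

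**A reader might infer that 65 per group also fails and that 66 (198 in all) is required.** The documents do not support that. The usual formula does round to 66, but the protocol speaks of about 10% dropout and sets 65 as a minimum. The difference is half a child per group, and power stays at 89.9% to 90.4%. With the effect size that the stated difference and SD actually give, 58 completers suffice and 65 recruited leaves 58.5.

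**A reader might treat the effect-size slip as a second power problem.** It is not. The stated 0.658 is the smaller value, so the slip makes the calculation slightly conservative.

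**Conclusion.** The recruitment total in the Overview contradicts the sample size requirement stated in the Overview and in section 6.1. The protocol's 59 and 65 per group are both sound for their purposes; the 177 is the figure that does not fit.

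The size is modest. Stopping at 177 with 10% loss costs about 3 to 3.5 points of power against the promised 90%. That rests on the protocol's own difference, SD and alpha of 0.025, on an unpaired t-test, and on dropouts adding no information. It does not mean that the trial as a whole is underpowered: the loss arises only if enrolment stops at 177 and dropout reaches the assumed level. The effect size of 0.658 is an arithmetic slip without consequence for this conclusion.

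**What to change.** State one enrolment figure in the Study population paragraph, the Overview sample size text and section 6.1. Either option resolves the contradiction:

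- **Keep 177.** Present it as 59 recruited per group, remove the minimum of 65, and restate power as about 87% at two-sided alpha 0.025 after 10% loss. This needs no extra children and costs only a less favourable power statement.
- **Use the protocol's own requirement.** Change 177 to 195 (65 per group). This keeps the 90% claim to within rounding and adds 18 children to the Overview total, 12 of them in the primary comparison. There is no need to go to 198.

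In the same edit, make the effect size agree with its inputs: either 0.663 with an SD of 0.475 D, or 0.658 with an SD of 0.479 D. If 0.663 is chosen, the required numbers become 49 and 58, and 65 per group after the dropout allowance is unchanged. This is a text correction in both places.

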## **Sites of the study**

Optometry Research Clinic, School of Optometry, PolyU

**Inclusion criteria**

- Hong Kong Chinese
- Age at enrolment: 4-12 years
- Myopia (in spherical equivalent refraction, SER)  $-0.75\text{D}$  or below in both eyes
- Documented evidence of fast progressing myopia in the last 2 years, either in SER or axial length (AL) (Details in Section 5.1):
  - SER progression:  $0.50\text{D}/\text{year}$  or more in either one eye or both eyes
  - AL elongation:  $0.27\text{mm}/\text{year}$  or more in either one eye or both eyes
- For children aged 4-6 years without past prescription forms, eligibility requires myopia below the 3rd percentile on refraction curves:
  - 4-5 years old: myopia of  $-0.75\text{D}$  or below in both eyes
  - 6 years old: myopia of  $-1.25\text{D}$  or below in at least one eye, with the other eye  $-0.75\text{D}$  or below
- Best-corrected visual acuity (BCVA) in both eyes matches age norms:
  - 4-6 years old:  $0.20 \log\text{MAR}$  (or its equivalent) or better
  - 7-12 years old:  $0.00 \log\text{MAR}$  (or its equivalent) or better
- Anisometropia of  $1.50 \text{ D}$  or less.
- Astigmatism of  $2.00 \text{ D}$  or less.
- Acceptance of random group allocation and the masked study design
- Able to wear the prescribed spectacle full-time

**Exclusion criteria**

- Existing or past eye diseases or surgeries (e.g., strabismus surgery, amblyopia, oculomotor nerve palsies, corneal disease, intraocular disease, etc.) that may have an impact on vision or visual development
- Binocular vision problems
- Long-term medication (intake at least 3 days/week)
- Medication or supplements that affect eye growth
- Systemic diseases that may have an impact on vision or visual development (e.g., endocrine, cardiac and respiratory diseases, diabetes, Down syndrome, etc.)
- Previous or current treatment for myopia control (e.g., orthokeratology, progressive addition lenses, myopic defocus lenses, atropine, etc)

- Allergies to topical anaesthetic or cyclopentolate eye drops
- Individuals who, in the judgment of the Investigator, are unable to cooperate and follow instructions during eye examination.

